### Measures

#### Personal Health Questionnaire-9 (PHQ-9)

PHQ-9 consists of the nine diagnostic criteria items for a MDE in the *Diagnostic and Statistical Manual of Mental Disorders, Fourth Edition* (DSM-IV), and the DSM-5 [28]. Each item is rated from 0 = *Not at all* through 3 = *Nearly every day*, with the total score ranging therefore between 0 and 27. The reliability and the validity of the original PHQ-9 and its Japanese version are well established [45, 46]. We used this scale successfully in our previous trial of the smartphone CBT [18].

#### Generalized Anxiety Disorder-7

GAD-7 was developed to measure the severity of generalized anxiety and consists of seven items representing nervousness, tension, and worrying [42]. Each item is rated from 0 = *Not at all* through 3 = *Nearly every day*, with the total score ranging therefore between 0 and 21. Its reliability and validity have been established [42]. The use of PHQ-9 and GAD-7 has been recommended as part of a standardized battery to measure health outcomes for depression and anxiety [47].

#### Big Five Scale of Personality Trait Adjectives

There are several validated scales to measure personality traits according to the five-factor model. We will use the short form of the Big Five Scale of Personality Trait Adjectives [37], commonly used in Japan. The reliability and validity of the short version have been ascertained [38]. Each of the five personality traits of neuroticism, extraversion, openness, agreeableness, and conscientiousness is measured with five to seven corresponding adjectives on a 5-point Likert scale from 0 = *Untrue of me* and 4 = *True of me*.

#### Autism Spectrum Quotient

The autistic trait of the participants will be measured with the short version of the Autism Spectrum Quotient, originally developed by Baron-Cohen et al. [48]. The reliability and validity of the Japanese version and its short from have been established [39].

#### Social Support Questionnaire

We will measure the size and quality of the students’ social support with the short form of the Social Support Questionnaire [40]. It measures the number of persons providing support and the satisfaction with such support in six domains. The reliability and validity of the original scale and its Japanese version have been satisfactory [40, 41].

#### Cognitive and behavioral skills

In order to measure each of the cognitive or behavioral skills for the five components to be examined in this trial in an efficient and valid manner, we have adopted the short versions based on the following established questionnaires. In order to measure the SM skill, we will use the five items that constitute the SM subscale of the original 17-item cognitive-behavioral self-monitoring scale developed by Tsuchida et al. [30]. The study confirmed the internal consistency reliability, factorial validity, and construct validity of the subscale. Each item is rated on a 4-point Likert scale from 0 = *Very untrue of me* through 3 = *Very true of me*, and the total score therefore ranges between 0 and 15.

The skills for CR will be measured with the six highest-loading items from the Competencies of Cognitive Therapy Scale, recently developed and validated by Strunk et al. [31]. Each item is rated from 0 = *Very untrue of me* through 3 = *Very true of me*, and the total score therefore ranges between 0 and 18. We ascertained the semantic equivalence between the Japanese version and its original English version through translation and back translation.

We will use the BA subscale of the Japanese Behavioral Activation for Depression Scale – Short Form, translated from the original English version [32] and validated in the Japanese population [33]. The Japanese version consists of five items, each rated from 0 = *Very untrue of me* through 3 = *Very true of me*.

AT will be measured by the self-assertion subscale of the Adult Social Skills Scale, developed by Aikawa et al. [34]. Its reliability, factorial validity, and construct validity have been established [34]. It consists of seven items, each rated between 0 = *Very untrue of me* through 3 = *Very true of me*.

The PS skill will be measured with the six highest-loading items of the approach avoidance style subscale of the Problem-Solving Inventory [35]. We developed its Japanese version through translation and back translation. The original study demonstrated the reliability, factorial validity, and construct validity for the original 32-item version. The reliability and validity of the abbreviated Japanese version need to be examined in this study. Each item is rated from 0 = *Very untrue of me* through 3 = *Very true of me*, and the total score ranges between 9 and 18.

#### CIDI

We will use the self-administered version of the Japanese WHO-CIDI 3.0 depression section [49, 50] to ascertain the diagnosis of a major depressive disorder according to DSM-IV in the past 12 months. The self-administered version has been shown to have good concordance with the clinical diagnosis of MDE [51] and to be reliable in a 1-year test–retest survey [44].

#### HPQ

We will use the three questions from the presenteeism subscale of the HPQ. The original study demonstrated its reliability and validity [36, 52]. The Japanese version of the HPQ has been used in the World Mental Health Survey in Japan [50].

### Participant timeline

Figure 2 shows the participant timeline, and Fig. 3 shows the enrollment, intervention, and assessment schedule.

**Fig. 2 Fig2:**
[figure not shown]
Enrollment, intervention, and assessment schedule

**Fig. 3 Fig3:**
[figure not shown]
Enrollment, intervention, and assessment schedule

### Sample size

The study will be powered for analysis 1 (i.e., those scoring 5 or more on baseline PHQ-9). The following sample size is therefore for this stratum. The sample size will be reviewed after the pilot run in the first year, which will inform us of the possible participation rate among university students. All the power calculations have been conducted with FactorialPowerPlan SAS Macro (available for free download at http://methodology.psu.edu).

In order to detect an effect size (standardized mean difference) of 0.20 for an efficacious component and their interaction at alpha = 0.05 and beta = 0.10 in analysis of covariance (ANCOVA), we need a total sample size of 1051. To reach this total sample size, the sample size for each of 64 combinations needs to be 17 and the total sample size is therefore 17 × 64 = 1088.

The mixed-effects repeated-measures analysis with more than 5 measurement points, planned for this trial, is known to require 30–50% fewer participants for the same power than a pre-to-post-only assessment [53]. Because we expect less than 30% dropouts, we conservatively set the final target sample size of our study as that calculated by usual ANCOVA-type power calculation without repeated measures and without dropouts as above.

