### Statistical methods

All analyses will be performed on the intention-to-treat sample.

#### Analysis 1 main analyses at week 8

We will use the mixed-effects repeated-measures analysis to estimate the mean difference in change scores on the PHQ-9 for each component. The model will include random effects for subjects (as intercepts) and fixed effects of treatment (main effects and second-order interaction effects of the five components), visit (as categorical), and treatment-by-visit interaction, adjusted for university, age, sex, and baseline PHQ-9 scores. Each of the experimental factors will be coded at two levels (presence coded as + 1 and absence as − 1) using effect coding. The primary outcome is change in PHQ-9 scores from baseline to week 8. The estimated mean differences will be converted into standardized mean differences by using the root of the variance taken from the covariance matrix. No adjustment for multiple testing will be applied in estimation of statistical significance of the main and interaction effects in this model, and the conventional threshold for statistical significance (*p* < 0.05, two-sided) will be used, because in the optimization phase of the MOST framework, the emphasis is on making a decision about what components will make up the optimized intervention [20], and factorial designs usually evaluate multiple completely different interventions that could have been assessed in separate trials and, conventionally, the multiple hypotheses have been tested independently in these trial designs [54, 55]. We will use a similar model for GAD-7 and cognitive and behavioral skills at week 8. As sensitivity analyses, we will repeat the above-mentioned analyses for the whole sample, including both strata scoring 4 or less and 5 or more on baseline PHQ-9. The most efficacious and efficient combination(s) of smartphone CBT for university students will be proposed on the basis of all the above findings.

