#### Analysis 1 secondary analyses

Exploratory analyses will be conducted to elucidate possible effect modification by the baseline variables on the efficacy of each component and of the proposed optimum combination(s) of components. The psychometric characteristics of the baseline questionnaires (internal consistency reliability, factor validity, and construct validity) will be ascertained. The ordering effect between BA and CR will be examined through comparison of the eight combinations in which CR comes before BA and the eight combinations in which BA comes before CR. The expected total sample size for this comparison is 272 (17 × 8 × 2). The comparison will have 70% power to detect an effect size of 0.3 at alpha = 0.05. Further exploratory analyses will be conducted on the mediator variables and use statistics of the smartphone CBT to examine the process of the therapy. Where repeated-measures analysis is not possible (e.g., cognitive behavioral skills), we will use multiple imputation for missing observations, where appropriate. The enduring effects of the 2-month intervention among those with elevated distress at baseline will be examined at week 52.

#### Analysis 2 main analyses at week 52

The primary outcome for analysis 2 is the incidence of a MDE by week 52 among all participants with or without elevated distress at baseline but without baseline MDE. We will use the mixed-effects logistic regression analysis to estimate the OR for each component. The model will include random effects for subjects (as intercepts) and fixed effects of treatment (main effects and second-order interaction effects of the five components), visit (as categorical) and treatment-by-visit interaction, university, age, sex, and baseline PHQ-9 scores.

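### The repeated-measures saving used to leave dropout out of the sample size does not apply to the week-8 contrast, so the 90% power holds only with week-8 data close to complete, unless a correlation the protocol does not state is credited

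*Protocol article*

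**What the plan says.** Protocol article, Sample size: the target effect is an "effect size (standardized mean difference) of 0.20 for an efficacious component" and for interactions, with alpha 0.05 and beta 0.10, in an ANCOVA-type calculation. The result is "we need a total sample size of 1051", raised to 17 × 64 = 1088. The section then says that a mixed-effects analysis with more than five measurement points needs 30–50% "fewer participants for the same power than a pre-to-post-only assessment". It expects dropout below 30% and concludes: "we conservatively set the final target sample size of our study as that calculated by usual ANCOVA-type power calculation without repeated measures", also without an allowance for dropout.

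Protocol article, Analysis 1 main analyses at week 8: the primary outcome is PHQ-9 change from baseline to week 8. The model has random subject intercepts, the component effects, visit as a category and "treatment-by-visit interaction, adjusted for university, age, sex, and baseline PHQ-9 scores". The test is two-sided at 0.05.

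Protocol article, Analysis 1 secondary analyses: for the BA/CR ordering comparison, with 272 participants expected, "The comparison will have 70% power to detect an effect size of 0.3".

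**The concern.** The argument sets a saving from repeated measures against a loss from dropout and treats the uninflated figure as the cautious choice. That works only if the saving exists for the contrast being tested. A saving of 30–50% is typical of an effect averaged over visits, or otherwise constrained to be common to them. The declared contrast is a single visit in a model that gives each visit its own treatment effect, and there the earlier visits have nothing to contribute until data go missing.

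The stake is the error rate of the selection step. Components are to be judged partly on p < 0.05. If power is below 90%, a component that truly has an effect of 0.20 is missed more often than the stated 10%, while the text tells the reader that the figure errs on the safe side.

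**Working it through.** **Inputs from the protocol.** SMD 0.20, two-sided alpha 0.05, power 90%, equal halves with and without a component, N = 1088, dropout below 30%, weekly PHQ-9 at weeks 1–8, random intercept (compound symmetry).

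**Inputs that are assumed.** The within-person correlation r after baseline adjustment and the timing of dropout are not given. I take r from 0.3 to 0.9.

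**1. Reproduce the plan's figure.** N = 4(1.960 + 1.2816)² / 0.20² = 1050.7, i.e. 1051. This uses SD = 1 and no reduction for a baseline covariate.

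**2. Power on week-8 completers.** Power = Φ(0.20·√N/2 − 1.960).

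| Missing at week 8 | Observed N | Power |
|---|---|---|
| 0% | 1088 | 91.0% |
| 10% | 979 | 87.9% |
| 20% | 870 | 83.9% |
| 30% | 762 | 78.8% |

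**3. Saving with complete data.** With a separate treatment effect at every visit and nobody missing, the generalized least squares estimate at week 8 is the plain week-8 difference. Its variance ratio to a single-visit comparison is 1.000 at every r tried, so the effective N is 1088 and the saving is zero. For the mean of eight visits the ratio is (1 + 7r)/8: 0.56 at r = 0.5 and 0.65 at r = 0.6, a saving of 44% and 35%. That is the order of saving the protocol quotes, but it belongs to a different contrast.

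**4. Recovery when data are missing.** Suppose a proportion d drops out after week k, missing at random. The variance ratio for week 8 is 1 + [d/(1 − d)]·(1 − R²), where R² = k·r²/(1 + (k − 1)r) is how well weeks 1 to k predict week 8. Example: d = 0.30, k = 7, r = 0.5 gives R² = 1.75/4 = 0.4375. The ratio is 1 + 0.4286 × 0.5625 = 1.241, effective N is 1088/1.241 = 877, and power is 84.2%. Evenly spread dropout was computed by adding the information over dropout weeks. Power at 30% missing:

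| r | All lost before week 1 | Evenly spread | After week 4 | After week 7 |
|---|---|---|---|---|
| 0.3 | 78.8% | 80.8% | 81.1% | 81.5% |
| 0.5 | 78.8% | 83.1% | 83.7% | 84.2% |
| 0.6 | 78.8% | 84.4% | 85.1% | 85.5% |
| 0.8 | 78.8% | 87.1% | 88.0% | 88.3% |
| 0.9 | 78.8% | 88.5% | 89.5% | 89.6% |

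No pattern tried, up to r = 0.9, reaches 90%.

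**5. Credit for baseline adjustment.** If 0.20 is on the unadjusted SD and ρ is the baseline/week-8 correlation, N in the power formula becomes 762/(1 − ρ²). Setting this equal to 1051 gives 1 − ρ² = 0.725, so ρ is about 0.52. On completers at 30% missing, power is 85% at ρ = 0.4, 89% at 0.5 and 93% at 0.6.

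**6. Ordering comparison.** Φ(0.30·√272/2 − 1.960) = 69.6%, which reproduces the stated 70% with all 272 observed. With 30% missing, 190 remain and completer power is about 54%.

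**The case against.** The best defence has four parts.

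First, 30% is a ceiling, not a forecast. The article describes a run-in before randomization, follow-up after stopping the intervention, reminders, and payment at weeks 4 and 8. It does not say whether the 30% refers to week 8 or to week 52. This stands: at 10% missing the loss against 90% is about two points even before any recovery.

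Second, earlier visits do help under dropout, and a high within-person correlation brings power close to 90%. This also stands. A reader might infer a fixed shortfall, such as a ceiling of 84% at 30% missing. The documents do not support that, because the correlation is not given and under the stated random-intercept model power passes 84% once r is about 0.6.

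Third, the calculation is called ANCOVA and the model adjusts for baseline, so the unadjusted-SD reading in step 5 could restore 90%. The text does not settle which SD defines 0.20. The rule of standardizing by the model covariance concerns reported estimates, and 1051 itself carries no baseline credit. This defence is available to the authors, but it is not the one they give.

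Fourth, the article openly says that its figure excludes dropout, and it plans a sample-size review after the pilot. That review is tied to the participation rate, not to dropout or correlation.

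None of this rescues the reason actually offered, which is a saving the declared contrast does not have.

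**Conclusion.** The point holds as a fault in the justification and in the stated power, not in the arithmetic of 1051 or in the analysis model. The repeated-measures offset should not be relied on for the week-8 contrast, and the uninflated figure is not conservative on that ground. With SD = 1, power is about 91% with complete week-8 data and 79% on completers at the 30% limit. With recovery from earlier visits it is about 80–85% at r of 0.3–0.6 and just under 90% at 0.9. The completer figures follow from the protocol's own inputs. The recovered figures rest on missing at random, compound symmetry and assumed values of r and dropout timing.

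Two stronger inferences are not supported. One is that the trial is certainly underpowered or must recruit more: actual dropout may be well below 30%, and a baseline correlation of about 0.52 on the unadjusted-SD reading would restore 90%. The other is that the ordering power is misstated: 70% is correct for 272 observed, and that section claims no offset for dropout.

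**What to change.** In Sample size, delete the repeated-measures offset and the word *conservatively*. State that 1088 gives about 91% power for an SMD of 0.20 with no missing week-8 data, and about 88%, 84% and 79% on completers at 10%, 20% and 30% missing. If recovery from earlier visits is credited, add the power under the planned model with the assumed within-person correlation and dropout pattern. If baseline adjustment is credited, state that 0.20 is on the unadjusted SD and give the assumed baseline/week-8 correlation. Optionally, note that the 70% for the ordering comparison assumes all 272 are observed.

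This changes wording only and adds no participants. The cost is a less favourable stated power. If the authors would rather guarantee 90% on completers at 30% missing, 1051/0.7 = 1502, i.e. 24 per combination or 1536 in total, is the price. The point does not require it.

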### Recruitment

In the first year of the study, we will conduct a pilot run aiming at enrolling 100–200 students at Kyoto University. This will inform us of the possible participation rate among the university students along with possible inadequacies and barriers in the protocol. In the second year of the study, depending on the findings from the pilot run, we will extend recruitment to other classes of undergraduate and graduate students at Kyoto University. In the third year of the study, depending on the recruitment so far, we will seek collaboration from several other universities in Japan. Recruitment from other universities may already be started in the second year.

#### Blinding

Neither the participant nor the study personnel will be blinded to the intervention that each participant is receiving through the conduct of the trial. The assessment of all the primary and secondary outcomes is self-report by the participant and therefore not blinded. The statisticians will be blinded to the allocation through the statistical analyses by analyzing the datasets prepared by the study personnel in which all components are denoted only by a letter. The writing committee will review the statistical analysis report without knowledge of the identification of the components, which will be revealed only after the writing committee signs off the agreed-on statement of interpretation.

### Data collection, management, and analysis

#### Data collection methods

All the data will be collected via the smartphone app platform.

#### Plans to promote participant retention and complete follow-up

The outcome data will be collected even when the participant has not completed the allocated intervention, unless he/she has expressed a wish to completely withdraw from the study. When the participant fails to fill in the scheduled assessments, reminders will be sent in 24 hours and 48 hours via automated popup on the smartphone. If the participant still has not filled in the assessment, a semiautomated email will be sent once as a gentle reminder. No further attempt will be made for that assessment. The participants will receive modest compensation for the time it requires to fill in the questionnaires: 1000 yen when they complete week 4 assessment, 2000 yen when they complete week 8 assessment, and 2000 yen when they complete week 52 assessment.

#### Data management

A secure, web-based, password-protected database will be used to manage recruitment, eligibility assessment, randomization, scheduling and tracking, baseline and follow-up assessments, and delivery of the allocated interventions. All the assessment data will be checked automatically for integrity by this platform. The security of the data transfer between the app and the server will be guaranteed through the Secure Socket Layer (SSL).

### Statistical methods

All analyses will be performed on the intention-to-treat sample.

#### Analysis 1 main analyses at week 8

We will use the mixed-effects repeated-measures analysis to estimate the mean difference in change scores on the PHQ-9 for each component. The model will include random effects for subjects (as intercepts) and fixed effects of treatment (main effects and second-order interaction effects of the five components), visit (as categorical), and treatment-by-visit interaction, adjusted for university, age, sex, and baseline PHQ-9 scores. Each of the experimental factors will be coded at two levels (presence coded as + 1 and absence as − 1) using effect coding. The primary outcome is change in PHQ-9 scores from baseline to week 8. The estimated mean differences will be converted into standardized mean differences by using the root of the variance taken from the covariance matrix. No adjustment for multiple testing will be applied in estimation of statistical significance of the main and interaction effects in this model, and the conventional threshold for statistical significance (*p* < 0.05, two-sided) will be used, because in the optimization phase of the MOST framework, the emphasis is on making a decision about what components will make up the optimized intervention [20], and factorial designs usually evaluate multiple completely different interventions that could have been assessed in separate trials and, conventionally, the multiple hypotheses have been tested independently in these trial designs [54, 55]. We will use a similar model for GAD-7 and cognitive and behavioral skills at week 8. As sensitivity analyses, we will repeat the above-mentioned analyses for the whole sample, including both strata scoring 4 or less and 5 or more on baseline PHQ-9. The most efficacious and efficient combination(s) of smartphone CBT for university students will be proposed on the basis of all the above findings.

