#### Secondary outcomes

The secondary outcomes are as follows:PHQ-9 at weeks 1, 2, 3, 4, 5, 6, 7, 12, 16, 20, 24, 28, 32, 36, 40, 44, 48, and 52Generalized Anxiety Disorder-7 (GAD-7) at weeks 4, 8, and 52Cognitive and behavioral skills [30–35] at weeks 8 and 52Presenteeism scale from the Health and Work Performance Questionnaire (HPQ) [36] at weeks 8 and 52Use statistics of the smartphone app through the trialCointerventions (visits to a mental health professional, psychotropics, counseling/psychotherapy)

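### The primary model's only stated covariance term is a subject random intercept, so the week-8 standard error is borrowed from all weeks and may be wrong in either direction

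*Protocol article*

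**What the plan says.** Under Statistical methods (Analysis 1 main analyses at week 8), the covariance part of the model is described in one place: "The model will include random effects for subjects (as intercepts) and fixed effects of treatment". The fixed part also contains "visit (as categorical), and treatment-by-visit interaction, adjusted for university, age, sex, and baseline PHQ-9 scores", so the mean is free at each visit for each component level. The same paragraph sets the endpoint: "The primary outcome is change in PHQ-9 scores from baseline to week 8". Each effect is judged at the conventional level (p "< 0.05, two-sided) will be used"), without multiplicity adjustment.

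Under Secondary outcomes, PHQ-9 is also collected weekly before the primary time point ("PHQ-9 at weeks 1, 2, 3, 4, 5, 6, 7, 12" and later). With week 8, that gives eight post-baseline visits in the analysis window.

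The estimated differences are then "converted into standardized mean differences by using the root of the variance taken from the covariance matrix". The text does not say which matrix or which visit is meant. Nothing in the article mentions visit-specific variances, another residual structure or robust standard errors.

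**The concern.** The model lets the mean differ by week but, on its ordinary reading, not the variance or the correlation. A random intercept with independent, homogeneous residuals is compound symmetry. The decision on each component rests on one visit, yet the precision of that visit's contrast is estimated from the average over all eight.

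There are two ways for this to go wrong. First, the week-8 variance may differ from the average. The model adjusts for baseline PHQ-9, and the correlation of a score with baseline usually fades, so variance given baseline can grow with time. Second, correlations between weeks usually decay with distance. A constant correlation then misstates how much a dropout's earlier scores tell us about week 8.

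At stake is whether the p values and confidence intervals behind keeping or dropping a component have their nominal properties. The plan tests five main effects and their two-way interactions unadjusted, so nothing absorbs a shift in per-test error.

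**Working it through.** **The plan's own figure.** The Sample size section plans for a standardized mean difference of 0.20 and reports the result as follows: "at alpha = 0.05 and beta = 0.10 in analysis of covariance (ANCOVA), we need a total sample size of 1051". The normal approximation gives 4 × (1.96 + 1.2816)² / 0.20² = 1050.7, which matches 1051. Then 1051 / 64 = 16.4, rounded up to 17, and 17 × 64 = 1088. The sample size reproduces and is not affected by this point.

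**Inputs.** From the protocol: eight weekly visits, baseline as covariate, two-sided alpha 0.05, N = 1088, dropout expected to stay below 30%. Assumed, because the article gives none: visit SDs, correlations with baseline, correlations between weeks, and the dropout pattern.

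**Complete data, closed form.** With free visit and treatment-by-visit means, the week-8 estimate is the same as from a week-8 comparison, but its standard error uses the average variance:

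- ratio = model SE / true SE = √(mean conditional variance over weeks 1-8 / conditional variance at week 8)
- actual alpha = 2 × (1 − Φ(1.96 × ratio))
- conditional variance at a visit = SD² × (1 − r²), where r is the correlation with baseline

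Example: SD constant at 1 and r falling linearly from 0.8 to 0.5. The conditional variances are 0.360, 0.427, 0.490, 0.549, 0.605, 0.657, 0.705 and 0.750, with mean 0.568. The ratio is √(0.568 / 0.750) = 0.870. Alpha is 2 × (1 − Φ(1.705)) = 8.8%.

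| Assumed path, week 1 to week 8 | SE ratio | Actual alpha |
|---|---|---|
| SD flat, r 0.8 to 0.5 | 0.87 | 8.8% |
| SD flat, r 0.7 to 0.5 | 0.92 | 7.1% |
| SD flat, r 0.6 to 0.5 | 0.96 | 5.9% |
| SD flat, r constant | 1.00 | 5.0% |
| SD falls 20%, r 0.8 to 0.5 | 0.97 | 5.9% |
| SD falls 20%, r 0.7 to 0.5 | 1.03 | 4.4% |
| SD falls 20%, r 0.6 to 0.5 | 1.08 | 3.4% |

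**Simulation check** (N = 1088, 6,000 trials per setting). With flat SD and r from 0.8 to 0.5, the empirical SE was 0.0270, the model SE 0.0233 and the rejection rate 8.9%. With r from 0.7 to 0.5, rejection was 7.5%. With equal variances and correlations it was 5.0%. With SD falling 20% and r from 0.7 to 0.5 it was 4.5%. One actual mixed-model fit in the first setting gave a week-8 SE of 0.0233, against 0.0261 from week-8 ANCOVA on the same data.

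**With dropout.** Here the model-based variance was compared with the sandwich variance of the week-8 contrast. The assumptions were 30% monotone random dropout spread evenly over the weeks and AR(1) correlation 0.85; the SDs are those given baseline.

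| SD path | No dropout | 30% dropout |
|---|---|---|
| Flat | 5.0% | 6.6% |
| 3.0 to 3.5 | 6.8% | 8.8% |
| 3.5 to 3.0 | 3.4% | 4.7% |

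A milder correlation decay with flat SD and dropout gives 5.6%. The 30% is the upper end of what the protocol expects, so these are upper figures for that pattern.

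**SMD divisor.** Under the stated model, the variance is adjusted for baseline and pooled over weeks. Adjustment alone makes the SMD larger than one based on the raw SD by 1/√(1 − r²): 5% at r = 0.3 and 25% at r = 0.6. Pooling multiplies it by a further 1/ratio, for example 1/0.87 = 1.15 in the first row of the complete-data table.

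**The case against.** The strongest reply is that the article never states the residual structure. Equal variance follows only if the residuals are independent and homogeneous, and the reference to a covariance matrix could point to a richer structure in a fuller document that is not shown. This stands as a condition on the finding. It does not remove it: the random intercept is a stated choice, and the ordinary meaning of that choice alone is compound symmetry.

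A reader might also infer that week 8 has the largest variance, and hence that the standard error is certainly too small and components will be kept too often. The documents do not support that. They give no SDs or correlations. PHQ-9 has a floor at 0, scoring 10 or more at screening excludes, and scores are expected to fall, so the spread may shrink. The test is then conservative in several settings above. Larger figures, such as 11.4% for an SD rising from 2.5 to 4.0, need a 2.56-fold rise in variance that has no source.

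On the SMD, a reader might infer that reported effects will look larger than the 0.20 used for planning. That does not follow. The 0.20 was set for ANCOVA and can be read in units of the ANCOVA error SD, in which case a baseline-adjusted divisor matches it. Entry limits also restrict the baseline range, which lowers the correlation and the inflation. Inflation of 35-61% would require dividing by the intercept variance alone, which nothing in the text suggests. The divisor changes no test.

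Finally, the combination will be proposed from several findings together, and a later evaluation trial is expected. That limits the harm from a drift of a few points, but does not justify an avoidable one.

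**Conclusion.** The point holds in conditional form. On its ordinary reading, the stated model ties the week-8 standard error to a variance pooled over weeks 1 to 8 and to one common correlation. That standard error is correct only if variances are equal across weeks and, once there is dropout, correlations are equal too; otherwise it could be right only by chance offset.

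Actual alpha is about 6-9% if variance given baseline rises to week 8 as assumed, about 6-7% with flat variance, decaying correlation and 30% dropout, and about 3-5% if the spread shrinks. The mechanism is certain under homogeneous residuals; the direction is not fixed by the documents. The change is worth making before analysis, but the fault does not undermine the design or the sample size. The unnamed SMD divisor is a secondary matter of interpretation.

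**What to change.** Replace the subject random intercept with an unstructured, visit-specific covariance over weeks 1 to 8. That is 8 × 9 / 2 = 36 parameters, feasible with about 1,000 participants. In the complete-data settings above, it brings the ratio to 1 and alpha to 5%, whether the variance rises or falls. Pre-specify what happens if the model does not converge, for example a simpler heterogeneous structure with robust standard errors.

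State that the standardized mean difference divides the week-8 difference by a week-8 SD, and say which one (for example, the observed pooled SD of week-8 PHQ-9).

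Kenward-Roger degrees of freedom and a baseline-by-visit term are optional refinements. The cost is a few lines of protocol or SAP wording and the need for the convergence fallback. No data collection changes.
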